## Abstract

**Background:**

Group A streptococcus is found in 20–40% of cases of childhood pharyngitis; the remaining cases are viral. Streptococcal pharyngitis (“strep throat”) is usually treated with antibiotics, while these are not indicated in viral cases. Most guidelines recommend relying on a diagnostic test confirming the presence of group A streptococcus before prescribing antibiotics. Conventional first-line tests are rapid antigen detection tests based on throat swabs. Recently, rapid nucleic acid tests were developed; they allow the detection of elements of the genome of group A streptococcus. We hypothesize that these rapid nucleic acid tests are sensitive enough to be performed on saliva samples instead of throat swabs, which could be more convenient in practice.

**Methods:**

This is a multicenter, prospective diagnostic accuracy study evaluating the performance of a rapid nucleic acid test for group A streptococcus (Abbott ID NOW STREP A2) in saliva, compared with a conventional pharyngeal rapid antigen detection test (EXACTO PRO STREPTATEST, lateral flow assay, comparator test), with a composite reference standard of throat culture and group A streptococcus PCR in children with pharyngitis in primary care (i.e., 27 primary care pediatricians or general practitioners). To ensure group A streptococcus is not missed, the salivary rapid nucleic acid test requires a minimally acceptable value of sensitivity (primary outcome) set at 80%. Assuming 35% of participants will have group A streptococcus, we will recruit 800 consecutive children with pharyngitis. Secondary outcomes will include difference in sensitivity between the pharyngeal rapid antigen detection test and the salivary rapid nucleic acid test; variability in sensitivity and specificity of the salivary rapid nucleic acid test with the level of McIsaac score; time to obtain the result of the salivary rapid nucleic acid test; patient, physician, and parents satisfaction; and barriers and facilitators to using rapid tests for group A streptococcus in primary care.

**Ethics and dissemination:**

Approved by the Institutional Review Board “Comité de protection des personnes Ile de France I” (no. 2022-A00085-38). Results will be presented at international meetings and disseminated in peer-reviewed journals.

**Trial registration number:**

ClinicalTrials.gov: NCT05521568.

## Introduction

Acute pharyngitis is responsible for 15 million visits to physicians each year in the USA [1]. Group A streptococcus is found in 20 to 40% of cases of childhood pharyngitis (37% in a recent meta-analysis) [2]; the remaining cases are viral. Streptococcal pharyngitis (“strep throat”) is usually treated with antibiotics to accelerate symptom relief, prevent complications, and reduce the spread of group A streptococcus [3, 4], while antibiotics are not indicated in viral cases. Because signs and symptoms of streptococcal and viral cases overlap, diagnosing streptococcal pharyngitis on clinical grounds is considered unreliable, even for expert clinicians, and most pediatric guidelines recommend relying on a diagnostic test confirming the presence of group A streptococcus to select who should receive antibiotics [1, 5]. The usual reference standard test for diagnosing streptococcal pharyngitis is a throat culture in the microbiology laboratory using a throat swab. However, throat culture is impractical for routine care because the result is only available after 24–48 h [6].

Rapid antigen detection tests have been developed since the 1980s. They provide a result within minutes and can be performed at the point of care. Several studies and meta-analyses have evaluated rapid antigen detection tests in children with pharyngitis and shown that they allow diagnosis with high sensitivity (86% on average) and high specificity (95% on average) [7], which is better than clinical scoring systems (e.g., Centor and McIsaac scores) [8]. In many countries, recommendations are to prescribe antibiotics only with a positive rapid antigen detection test result. Several randomized trials and meta-analyses have shown that implementing rapid antigen detection tests significantly reduces antibiotic prescriptions by 25 percentage points on average [9]. Despite their acceptable diagnostic accuracy, substantial impact on antibiotic use, and low cost (i.e., about US $1/test), there is still a failure in implementing rapid antigen detection tests. For example, according to the latest study in primary care in France, including more than 200,000 general medicine consultations, the antibiotic prescriptions rate in French children with pharyngitis in general practice was 67% [10]. The main reasons cited by primary care physicians for not performing rapid antigen detection tests are lack of time and difficulty in performing them. One of the main limitations of current rapid antigen detection tests, particularly in children, is the need for a throat swab. In a recent evaluation, the sensitivity of a rapid antigen detection test varied from 56 to 96% among physicians, and this was likely due to a suboptimal throat swab technique [11]. Another limitation of pharyngeal rapid antigen detection tests is that pharyngeal swabbing may cause the patient to cough, potentially contaminating the people and the environment in the room.

Since the 2010s, rapid nucleic acid tests for group A streptococcus that use polymerase chain reaction (PCR) and other nucleic acid amplification techniques have been available [12]. They have the advantage of being very sensitive and able to give a result within minutes. Some of these tests seem simple, compact, and quick enough to be implemented in primary care [13]. A recent meta-analysis showed that these rapid nucleic acid tests for group A streptococcus have a sensitivity of 97.5% with a specificity of 95.1% on average [14]. A North-American pilot study conducted on 20 patients showed that a rapid nucleic acid test for group A streptococcus (Roche’s cobas Liat test) could be performed on saliva with satisfactory performance and results highly consistent with those of a conventional pharyngeal rapid antigen detection test [15]. Replacing conventional pharyngeal rapid antigen detection tests with less invasive salivary rapid nucleic acid tests would allow for keeping the benefits of rapid tests while avoiding the throat swab step.

Here, we will carry out the first large-scale study to evaluate the diagnostic accuracy of a rapid nucleic acid test for group A streptococcus on saliva in children with pharyngitis in primary care. We will also compare the accuracy of the salivary rapid nucleic acid test to that of the rapid antigen detection test that is currently used in routine care.

## Materials and methods

### Study objectives

The primary objective of this study is to evaluate the sensitivity of a rapid nucleic acid test for group A streptococcus on saliva in children in primary care.

Secondary objective(s) include the following:To compare the diagnostic accuracy of the salivary rapid nucleic acid test versus that of a conventional pharyngeal rapid antigen detection test (EXACTO PRO STREPTATEST, a lateral flow assay)To evaluate the variability in diagnostic accuracy of the salivary rapid nucleic acid test according to the clinical severity of patients (“spectrum effect”)To evaluate the barriers and facilitators to using rapid tests for group A streptococcus in primary careTo evaluate the satisfaction of physicians and users (children and their parents)

### Study design

This is an observational, prospective, multicenter, cross-sectional, comparative, single-gate, double-blinded, manufacturer-independent diagnostic accuracy study.

### Study setting

The study will be conducted in 27 private practices of general practitioners and pediatricians in France. If necessary, further practices may be included to ensure recruitment within the intended time frame.

### Eligibility criteria

#### Inclusion criteria

Children 3–15 yearsManaged in primary care by a general practitioner or primary care pediatricianWith a clinical diagnosis of acute pharyngitis, defined as an inflammation of the pharynx and/or tonsils (i.e., erythema with or without exudate) or acute sore throat (even if without local signs of pharyngeal inflammation)Non-opposition of the accompanying parent(s)

#### Exclusion criteria

Children who received antibiotics within 7 days before potential inclusionChildren already enrolled in the study for the same episode of pharyngitis

### Recruitment

Children with acute pharyngitis will be recruited consecutively from 27 primary care private practices throughout France over a period of 18 months. Recruitment is expected to start in the first trimester of 2023.

### Data collection

Data collection procedures and timing are described in Table 1. First, physicians will collect sociodemographic and clinical data. Second, they will perform the salivary rapid nucleic acid test (index test). Third, they will take a throat sample for the reference standard and the comparator test.

**Table 1 Tab1:** Data collection procedures and timing

Type of data	Inclusion visit	One-month follow-up phone call	After the end of patient inclusions
Baseline information			
Non-opposition to participate in the study	X		
Sociodemographic data	X		
Clinical data (including McIsaac criteria)	X		
Biospecimens			
Saliva sample (for the salivary rapid nucleic acid test)	X		
Double throat swab (one for the pharyngeal rapid antigen detection test, one for the composite reference standard)	X		
Test results			
Result of the salivary rapid nucleic acid test (index test)^a^	X		
Result of the pharyngeal rapid antigen detection test (comparator test)^a^	X		
Result of group A streptococcus culture and group A streptococcus PCR (reference standard)^b^	X		
Satisfaction			
Patient satisfaction (Likert)	X		
Physician satisfaction (Likert)	X		
Parent satisfaction (Likert)	X		
Antibiotic prescription	X		
Clinical evolution (i.e., whether the episode of pharyngitis healed, worsened, or relapsed)		X	
Qualitative survey for participating physicians (i.e., barriers and facilitators regarding the use of rapid tests)			X^c^

*PCR* Polymerase chain reaction

^a^Performed at the point of care

^b^Performed in the microbiology laboratory

^c^Each participating physician will take the survey once

### Clinical data and data storage

For each participant, the following information will be collected using an online case report form (eCRF):Patient ageMcIsaac score criteriaResult of the salivary rapid nucleic acid test (saliva swab)Result of the pharyngeal rapid antigen detection test (throat swab)Time to obtain the result of the rapid nucleic acid test (measured by the clinician in charge, using a chronometer, a watch, or a smartphone)Antibiotic prescription (yes/no and details if antibiotics are prescribed)Patient satisfaction (Likert scale) regarding the pharyngeal rapid antigen detection test and the salivary rapid nucleic acid testPhysician satisfaction (Likert scale) regarding the pharyngeal rapid antigen detection test and the salivary rapid nucleic acid testParent satisfaction (Likert scale) regarding the pharyngeal rapid antigen detection test and the salivary rapid nucleic acid testOne-month follow-up phone call (whether the episode healed, worsened, or relapsed)

Anonymized data will be stored on a secured server for 15 years after the completion of the study.

### Index test

The test under evaluation (“index test”) is the rapid nucleic acid test for group A streptococcus Abbott ID NOW STREP A 2 (formerly known as Alere i strep A test; Fig. 1), performed on saliva samples instead of throat swabs. This rapid nucleic acid test was chosen because of its ease of use and several previous evaluations showing high diagnostic accuracy on throat swabs [16–18]. The ID NOW STREP A 2 does not rely on a rapid PCR technique but is based on the principle of isothermal nicking enzyme amplification reaction. It allows rapid detection of group A streptococcus nucleic acids by amplifying a sequence of the *cepA* gene, which encodes the C5a peptidase, an important streptococcal virulence factor. The swab to be tested is directly inserted into the platform for 10 s, without any complex steps. The ID NOW STREP A 2 test gives a binary result after 2 to 6 min. The rapid nucleic acid test will be performed at the point of care by participating primary care practitioners, using salivary swabs instead of throat swabs. Saliva samples will be collected using the swabs provided by Abbott in the test kits. Children will be invited to suck on the swab for 30 s as they would for a lollipop. In a preliminary study, we tested the swab with saliva from asymptomatic volunteers and found no inhibitor; the test also proved able to detect group A streptococcus when testing three strains of group A streptococcus with progressive dilutions (see Appendix 1). Rapid nucleic acid test results will not be used for patient management. Clinicians performing the saliva rapid nucleic acid test will be blinded to the result of the reference standard and the result of the pharyngeal rapid antigen detection test but not to clinical information. Participating practitioners will receive specific training before the study.

**Fig. 1 Fig1:**
[figure not shown]
Abbott’s ID NOW STREP A 2 (rapid nucleic acid test)

### Reference standard

The reference standard will be a composite of culture and group A streptococcus PCR, using a throat swab. Throat culture is the most accepted reference standard for diagnosing strep throat. However, studies have shown that culture may be falsely negative in the presence of other bacteria, such as *Staphylococcus aureus*, and in such cases, group A streptococcus PCR would be positive elsewhere [19]. Throat samples will be obtained by use of a double-swab collection-transportation system (COPAN Diagnostics, Corona, CA, USA). Swab no. 1 will be used immediately to perform the pharyngeal rapid antigen detection test (see below), as per usual care. Swab no. 2 will be put in the Amies agar transportation system, held at ambient temperature, and sent within 72 h to the Robert Debre Hospital microbiology laboratory by an express messenger service. Upon reception, throat swabs will be used to perform throat cultures using standard techniques, as described elsewhere [20]. Swab no. 2 will also be used to perform a group-A-streptococcus-specific PCR, as described elsewhere [19]. Samples with a positive culture and/or a positive PCR test result will be classified as group A streptococcus positives. Samples with a negative culture and a negative PCR will be classified as group A streptococcus negatives. Executors of the reference standard will be blinded to clinical data, including the result of the pharyngeal rapid antigen detection test and salivary rapid nucleic acid test.

### Comparator test

As per usual care, all children will undergo a conventional pharyngeal rapid antigen detection test, using swab no. 1 (see above). This lateral flow assay is the one used in France and is the only commercial kit that is officially recommended by the National Health Insurance system. It detects Lancefield’s group A antigen, which is specific to group A streptococcus and provides a binary result. The test will be performed at the point of care by primary care practitioners participating in the study, as per usual care. Clinicians performing the rapid antigen detection test will not be blinded to clinical information and results of the salivary rapid nucleic acid test.

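### The antigen test is performed by clinicians who may already know the salivary result, so the secondary paired comparison is at risk of review bias of unknown size and direction

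*Protocol article*

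**What the plan says.** Study design describes a "single-gate, double-blinded, manufacturer-independent diagnostic accuracy study" and does not say who is blinded to what. The later sections do:

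- **Index test:** "Clinicians performing the saliva rapid nucleic acid test will be blinded to the result of the reference standard", and also to the antigen result, though not to clinical information. The instrument returns a binary result after 2 to 6 minutes.
- **Reference standard:** the laboratory is blinded to clinical data and to both rapid tests.
- **Comparator test:** "Clinicians performing the rapid antigen detection test will not be blinded to clinical information and results of the salivary rapid nucleic acid test". The test is a lateral flow assay with a binary result, run by the participating practitioner at the point of care.

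Data collection fixes the order. Clinical data come first and the salivary test second. Then: "Third, they will take a throat sample for the reference standard and the comparator test".

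Under Diagnostic accuracy, the sensitivity and specificity of the two tests are compared by McNemar's test on paired data. Comparing the accuracy of the two tests is the first secondary objective, and the difference in sensitivity is the first secondary outcome.

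**The concern.** Two tests are compared in the same child, and the one done second may be carried out with the first result known. The index test is protected from the antigen result, but the antigen test is not protected from the index result. The index result comes from an instrument, which leaves little room for judgement. The antigen test depends more on its operator: the Introduction cites an evaluation in which its sensitivity ranged from 56 to 96% among physicians, probably because of swab technique.

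At stake are the antigen test's own sensitivity and specificity and the paired difference from the salivary test. The Introduction promises a comparison with the antigen test as used in routine care. Knowing the clinical picture is part of routine care, but knowing a salivary nucleic acid result is not. A reader of Study design alone would also assume that the comparison was blinded.

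**Working it through.** **Blinding, direction by direction**

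| Test performed | Blinded to reference | Blinded to the other rapid test |
|---|---|---|
| Salivary test (Index test) | yes | yes |
| Reference standard | – | yes, both rapid tests |
| Antigen test (Comparator test) | not stated | no |

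Index test and reference standard are blinded to each other. The antigen test is not blinded to the salivary test, and that pair is the one McNemar's test compares.

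**The plan's own figure.** The sample size is not in dispute. Power is not stated; 80% reproduces the figure: (1.960 + 0.842)² × 0.86 × 0.14 / 0.06² = 262.5, so 263 cases, and 263/0.35 = 751. The antigen reading does not enter this calculation.

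**Illustration of size.** The protocol gives no rate of influenced readings, so every *q* below is assumed.

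Inputs: sensitivity of 86% for both tests (Sample size calculation expects 86% for saliva and assumes equality), and 263 cases. Let *a* be the share of antigen-missed cases that are saliva-positive.

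1. *One-directional pull.* A share *q* of negative antigen results in saliva-positive cases becomes positive. Antigen sensitivity = 0.86 + 0.14 × *a* × *q*.
   - *a* = 0.60 (assumed), *q* = 0.20: 0.86 + 0.0168 = 87.7%.
   - *a* = 0.86 (independent misses), *q* = 0.20: 0.86 + 0.0241 = 88.4%.
   - In children: 263 × 0.14 × 0.86 = 31.7 discordant cases of this kind; 20% of them is about 6.
   - With *a* = 0.86 and *q* from 10 to 30%, antigen sensitivity is 87.2 to 89.6%. The difference (saliva minus antigen) is −1.2 to −3.6 points where the truth is 0. McNemar's test rejects in about 7 to 25% of studies instead of 5%.

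2. *Two-directional pull.* A share *q* of all discordant results is moved into agreement. Observed difference = (1 − *q*) × true difference. With equal sensitivities this is (1 − *q*) × 0 = 0, so no bias is expected in the difference.

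3. *Unequal sensitivities (assumed 86% saliva, 80% antigen, independent).* The discordant proportions are 0.86 × 0.20 = 0.172 and 0.14 × 0.80 = 0.112, a true gap of 6.0 points. For *q* from 10 to 30%:
   - two-directional: 0.9 × 6.0 = 5.4 down to 0.7 × 6.0 = 4.2 points;
   - one-directional: 0.9 × 0.172 − 0.112 = 4.3 points down to 0.7 × 0.172 − 0.112 = 0.8 points.

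4. *Specificity (assumed 95% for both, independent).* One-directional pull with *q* = 20% lowers antigen specificity by 0.20 × 0.05 × 0.95 = 0.0095, to about 94.05%.

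The result depends on the kind of pull and on the true accuracies. The difference can stay at zero, shrink, or move away from zero.

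**The case against.** The strongest reply is that this touches only a secondary comparison and is openly disclosed. That largely stands. The primary outcome is salivary sensitivity against culture and PCR. The antigen reading does not enter it, and the index operator and the laboratory are blinded to each other's results. *Double-blinded* can be defended in that narrow sense; it fails only for the comparator, which the label does not exclude.

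A reader might infer more than the protocol supports:

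- *That the comparison is biased, and towards no difference.* Under the equal sensitivity that the plan assumes, two-directional pull leaves the expected difference at zero and one-directional pull moves it away from zero. Only a risk of bias can be claimed.
- *That the strip is read by eye.* This is a fair inference from the assay format, but the protocol does not say it.
- *That the clinician sees the salivary result and then swabs more or less firmly.* The order of steps is given, but not whether the 2 to 6 minute result is awaited before swabbing. If it were, the reference swab, taken in the same double-swab act, could also be affected, because laboratory blinding does not cover sampling. The protocol does not establish this, so it cannot be counted as harm to the primary outcome.
- *That a 6-point gap between the tests is planned.* The only 6 points in the sample size section separate the 80% minimum from the 86% expected for saliva alone.

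It could also be said that reading the antigen test first only reverses the problem, because the operator would then know the antigen result when recording the index result. That is correct as far as it goes, and the remedy must deal with it. The exchange is still favourable, because an instrument readout leaves less room for judgement.

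**Conclusion.** The point holds as a risk of review bias in the secondary paired comparison of sensitivity and specificity, arising from a rule the protocol states outright. Its size and direction are unknown. Shifts of one to a few percentage points are plausible only under assumed rates of 10 to 30% and, for most figures, independence of the two tests. The primary outcome does not depend on the antigen reading, and the planned numbers stand. The blinding label under Study design and the rule under Comparator test need to be reconciled. This should be fixed, but it is not a reason to doubt the primary analysis.

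**What to change.** 1. **Procedure.** Keep saliva collection and the start of the ID NOW run first. Then take the throat swabs, and read and lock the antigen result in the eCRF before the ID NOW result is viewed.
2. **Comparator test.** State that the antigen test is performed and read without knowledge of the salivary result.
3. **Index test.** State that the salivary sample is collected and its run started before the antigen test, that the instrument generates the result, and that invalid or indeterminate runs are recorded as displayed. Without this edit, the present statement that the index operator is blinded to the antigen result would no longer be true.
4. **Study design.** Replace *double-blinded* with the blinding actually applied, test by test.
5. **Children already included.** Repeat the paired comparison in the subset read blind and report the unblinded reading as a limitation. If no such subset exists, only the limitation and the corrected wording remain possible, since analysis cannot recover a blinded reading.

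**Cost.** A change to the practice procedure, the training and the eCRF entry order, with no extra staff or samples. The clinician may wait a few minutes before viewing the salivary result, time to result must be taken at the end of the run rather than at viewing, and the index result is recorded with the antigen result known.
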